###### Mental health difficulties

2.3.4.2.12

A parent version of the Spanish-adapted Strengths and Difficulties Questionnaire (SDQ; Barriuso-Lapresa et al., 2014) will be used to evaluate mental health difficulties in children. This questionnaire comprises 25 items and utilizes a 3-point Likert scale. It assesses five dimensions of mental health: emotional problems, behavior problems, hyperactivity-inattention, problems with peers, and prosocial behavior. Parents will provide responses based on their observations of their children’s behavior over the past 6 months. The SDQ has moderate to good internal consistency, with Cronbach’s alpha values generally ranging from 0.50 to 0.83 across its subscales and total difficulties score.

###### School grades

2.3.4.2.13

An additional academic record will be acquired by gathering the most recent participants’ school grades. Grades in mathematics, Spanish language, Catalan language, and Physical Education will be collected, each scored on a scale from 0 to 10. Subsequently, the Grade Point Average (GPA) will be calculated as the overall average of these grades.

##### Confounding variables

2.3.4.3

###### Sociodemographic characteristics

2.3.4.3.1

Socioeconomic status of the children will be assessed using the Family Affluence Scale (FAS-II; Boyce et al., 2006), Version II, a validated instrument consisting of four items specifically designed for measuring socioeconomic status.

###### Parental education and occupation level

2.3.4.3.2

Parental educational levels will be assessed using a self-report questionnaire completed by both, of the participants’ parents. The questionnaire will include options such as “no elementary school,” “elementary school,” “middle school,” “high school,” and “university completed.” Additionally, the occupations of the participants’ parents will be categorized according to the International Standard Classification of Occupations (ISCO-08) developed by the International Labor Organization. This classification comprises 13 categories: Directors and managers, Scientific and intellectual professionals, Technicians and mid-level professionals, Administrative support personnel, Service workers and salespeople in shops and markets, Farmers and skilled agricultural workers, forestry, and fishing, Officers, operators, and artisans of mechanical arts and other trades, Plant and machine operators and assemblers, Elementary occupations, Military occupations, Housemaker, and Unemployment.

###### ADHD symptoms

2.3.4.3.3

A Spanish-adapted version of the ADHD Rating Scale-IV (Vallejo-Valdivielso et al., 2019), parent edition, will be used to gauge the frequency of symptoms linked to ADHD. This tool comprises 18 items, divided equally between inattention and hyperactivity, and employs a 3-point Likert scale. Parents will provide their assessments based on observations of their children’s behavior over the previous 6 months. The ADHD Rating Scale-IV parent edition shows excellent internal consistency, with Cronbach’s alpha values typically ranging from 0.86 to 0.96 across its subscales and total score.

#### Data analysis

2.3.5

Analyses of the outcomes will be conducted using linear mixed models in IBM SPSS Statistics for Windows, Version 20.0 (IBM, Armonk, New York, USA), with alpha levels set at *p* < 0.05. These models will evaluate the impact of the experimental condition (PA with cognitive engagement, PA without cognitive engagement, or cognitively engaging control), time (baseline, posttest 1, posttest 2, and posttest 3), group (with and without ADHD), and condition-by-group-by-time interaction. Random effects will be incorporated to address the clustered nature of the data. Furthermore, we will assess all assumptions and adjust our analyses for any necessary control variables.

### Phase II: school settings

2.4

#### Sample size and power

2.4.1

A between subjects, 2 conditions (video-based PA program, and control condition) × 2 times (pretest vs. posttest) repeated measures ANOVA design with 138 participants should be sufficiently powered to detect interactions at or above moderate effect sizes *f* = 0.25 which translates to an approximate Cohen’s *d* = 0.5 assuming alpha at 0.05, power at 80%, and a correlation among 2 repeated measures of 0.75. Considering these estimations, and a potential dropout rate of 10% observed in similar studies (Mora-Gonzalez et al., 2019), our investigation will recruit 600 participants.

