## Abstract

The Break4Brain project aims to elucidate the effects of both acute and chronic physical activity (PA) on educational achievement in children with and without Attention Deficit Hyperactivity Disorder (ADHD). This study will be conducted in two phases: a cross-over design followed by a hybrid type 1 implementation-effectiveness trial, which includes both a cluster randomized controlled trial (RCT) and a qualitative study. In phase I, 60 children aged 10–12, with 30 each from ADHD and non-ADHD groups, will participate in a laboratory-based study over 4 days within 1 month. They will participate in three counterbalanced experimental conditions: (i) PA with cognitive engagement, (ii) PA without cognitive engagement, and (iii) a cognitively engaging control. This phase will assess acute changes in brain function, academic performance, working memory, inhibitory control, and sustained attention. Phase II will involve 600 children aged 10–12, randomly assigned to either a video-based PA program or a control group (300 children per group) in an 8-week cluster RCT. This phase will also incorporate a qualitative approach to explore the implementation context through pre- and post-intervention semi-structured interviews with teachers and school staff, and questionnaires for students. The outcomes of interest in this phase will include working memory, cognitive flexibility, selective attention, and academic performance. For the cross-over study, we hypothesize that PA conditions will enhance the studied outcomes compared to the control condition. In the RCT, we anticipate that the 8-week active breaks program will result in significant improvements in the selected outcomes compared to the control group. This study is expected to make pioneering contributions by including novel variables and focusing on the ADHD population. Furthermore, if the cluster RCT proves effective, it could offer a practical and cost-effective resource for integrating active breaks into daily school routines.

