**Figure 1 fig1:**
[figure not shown]
Study design and sample size for phase I (cross-over study).

Concerning phase II (Figure 2A), measurements will be carried out in school settings. Participating schools will be randomly assigned to one of two experimental conditions (control: usual academic lessons; intervention: video-based PA program [physically active without cognitive engagement]). The intervention will take 8 weeks, with the intervention condition implemented daily during this period. To design the experimental condition, a qualitative design will be conducted (Figure 2B).

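### The Phase II sample size of 138 is not the answer for the two-arm school-randomised trial described, takes no account of clustering, and does not lead to 600

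*Protocol article*

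**What the plan says.** Section 2.4.1 of the protocol article describes a repeated measures ANOVA with two conditions and two times. It states that a "repeated measures ANOVA design with 138 participants should be sufficiently powered to detect interactions at or above moderate effect sizes", namely f = 0.25, equated with a Cohen's d of about 0.5. The remaining inputs are "assuming alpha at 0.05, power at 80%, and a correlation among 2 repeated measures of 0.75". From these estimates and "a potential dropout rate of 10% observed in similar studies", it concludes that "our investigation will recruit 600 participants".

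The design is described elsewhere. Section 2.1 says "Participating schools will be randomly assigned to one of two experimental conditions", section 2.4.2 repeats that schools are the unit of randomisation, and the Abstract refers to "a control group (300 children per group) in an 8-week cluster RCT". Section 2.4.6.1 plans a linear mixed model with condition, time and their interaction, and random effects for clustering by school.

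**The concern.** Section 2.4.1 gives a complete set of inputs, so 138 can be recomputed. Three things look wrong.

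- The number is larger than a two-group calculation with those inputs returns.
- The calculation treats children as independent, although whole schools are allocated and the planned analysis recognises this.
- The step from 138 to 600 is credited to a 10% dropout allowance that accounts for only a small part of it.

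This is the only power statement for Phase II. In a school-randomised trial, power is governed mainly by the number of schools and the ICC. If neither enters, a reader cannot tell what effect 600 children can detect, and a null result would be hard to interpret.

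**Working it through.** **Inputs from section 2.4.1:** k = 2 groups, m = 2 times, f = 0.25 (d about 0.5), alpha 0.05, power 80%, correlation r = 0.75, dropout 10%, recruitment 600.

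**1. Trying to reproduce 138 with independent children (noncentral F).**

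Between-group effect: λ = N f² m / [1 + (m − 1)r], with k − 1 and N − k degrees of freedom.
- Two groups, N = 112: λ = 112 × 0.0625 × 2 / 1.75 = 8.00, power 0.801. This is the smallest even N that reaches 80%.
- Two groups, N = 138: λ = 9.86, power 0.876.

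Condition-by-time interaction: λ = N f² m / (1 − r), with (k − 1)(m − 1) and (N − k)(m − 1) degrees of freedom.
- Two groups, N = 18: λ = 18 × 0.0625 × 2 / 0.25 = 9.0, power 0.804.
- Two groups, N = 138: λ = 69, power above 0.999.

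Reading the effect simply as d = 0.5 does not give 138 either. A two-sample t test needs 128. A change-score comparison needs 64 and a baseline-adjusted one 56 (normal approximation).

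Three groups, two times, between-group effect:
- N = 138: λ = 9.86 on 2 and 135 degrees of freedom, power 0.8002.
- N = 135: power 0.791.

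So 138 is exactly the three-group answer. The nearest two-group match at 80% power is 136, at alpha 0.025, which contradicts the stated 0.05.

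**2. From 138 to 600.** 138 / 0.9 = 153.3, so 154. In the other direction, 600 × 0.9 = 540 completers, and 540 / 138 = 3.91. That factor is not explained. Read as a design effect 1 + (n − 1)ICC for n pupils per school, it would imply an ICC of about 0.15 with n = 20, 0.12 with n = 25, or 0.06 with n = 50. These cluster sizes are assumed.

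**3. What clustering does.** The documents give no ICC or number of schools, so both are assumed here. With J schools and n = N/J pupils per school, the standard error in SD units is √(4 × [1 + (n − 1)ICC] / N), tested on J − 2 degrees of freedom. Baseline adjustment multiplies the variance by 1 − 0.75² = 0.4375, which takes the 0.75 to hold at school level as well.

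As an illustration of the 138 claim, take six schools of 23. The design effect is 1 + 22 × 0.05 = 2.1 at ICC 0.05 and 3.2 at ICC 0.10. Power at d = 0.5 is then 34% and 25% on the post-test alone, or 64% and 47% with baseline adjustment.

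For the recruited 600 with 540 completing (each cell shows ICC 0.05 / 0.10):

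| Schools (assumed) | Design effect | Power at d = 0.5, post-test only | Power at d = 0.5, baseline-adjusted | Detectable effect at 80% power, baseline-adjusted (SD) |
|---|---|---|---|---|
| 8 | 4.33 / 7.65 | 65% / 42% | 94% / 75% | 0.40 / 0.53 |
| 12 | 3.20 / 5.40 | 83% / 62% | 99% / 92% | 0.32 / 0.41 |
| 20 | 2.30 / 3.60 | 95% / 83% | >99.9% / 99% | 0.26 / 0.32 |

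**The case against.** The strongest reply is that no shortfall has been shown. For independent children, 138 is more than the stated inputs require, so that mismatch alone is a reporting defect. The trial recruits 600, not 138, so the six-school example describes a sample nobody will use. The planned model uses both pre-test and post-test, so the baseline-adjusted column is the more relevant one, and there five of the six scenarios detect 0.41 SD or less. The planned analysis does allow for school clustering. The three-group origin is inferred from a numerical match, since no three-arm Phase II is described. Finally, a condensed article may leave the number of schools to a fuller document or to a figure that is not shown.

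Much of this stands, and it limits the claim: 600 is not shown to be too few, and how 138 arose is not known. It does not rescue the section. The article prints inputs, a result and a conclusion that disagree with one another. A fuller document could add an ICC, but it could not make 138 the output of those inputs, nor make 138 with 10% loss equal 600.

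**Conclusion.** The concern holds on all three counts. With the stated inputs, two groups need 112 (between-group effect) or 18 (interaction). The figure of 138 coincides with a three-group between-group test, which is neither the two-arm design nor the interaction that the text names. No clustering term enters, although schools are randomised. Allowing for 10% dropout takes 138 to 154, leaving an unexplained factor of about 3.9 between 138 and the 540 expected to complete.

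These results need only the stated inputs and standard formulas. The cluster figures rest also on assumed ICCs of 0.05 to 0.10, assumed numbers of schools of equal size, and a baseline correlation of 0.75 at both levels. Over that range the 600 children could detect anything from 0.26 to 0.53 SD with baseline adjustment. That spread is what the present justification hides.

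**What to change.** Delete the sentence giving 138 and restate section 2.4.1 for the trial being run. State the two arms, the number of schools per arm, the expected pupils per school, an assumed ICC with a range, the design effect, schools minus 2 degrees of freedom, the baseline correlation and the 10% loss. Name the test being powered so that it agrees with the mixed model in section 2.4.6.1. Then report the effect that the fixed 600 children can detect at 80% power across the ICC range.

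The cost is a rewording and a short recalculation, with no extra children. The detectable effect may look less favourable than the present text suggests. Section 2.4.2 describes recruitment as ongoing, so if the number of schools is still open, the recalculation is most useful now.

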#### Recruitment and randomization

2.4.2

Recruitment primarily involves contacting to schools in the Balearic Islands via email. The email addresses of each primary school were acquired from the Spanish Ministry of Education website. Once recruited, an initial virtual meeting was made to explain the study’s objectives. Figure 3 illustrates the flow diagram of the participant’s recruitment process. Recruitment began in March 2024 and is still ongoing. Once teachers and parents agree to participate, they sign a written informed consent form before the start of the intervention. In line with phase I, this study will also obtain verbal assent from participating children. Only those who provide verbal agreement, having fully understood the study’s aims and procedures, will be included.

**Figure 3 fig3:**
[figure not shown]
Flow diagram of the participant’s recruitment process.

Randomization of schools into experimental conditions for phase II is carried out using R software by an external statistician.

#### Experimental protocol

2.4.3

The experimental protocol will be composed of two parts: (a) qualitative: the experimental condition will be developed through a qualitative design involving semi-structured interviews with teachers and school staff, along with semi-structured questionnaires administered to students (Figure 2B). The same process will be replicated after the intervention; (b) quantitative: the intervention will be implemented within school settings during regular curricular hours, taking place inside the classroom (Figure 2A). Specifically, schools randomly selected and assigned to the research arms (video-based PA program, or control condition) will conduct educational achievement assessments twice, separated by 8 weeks. The initial assessment will occur at the pretest stage (week 1), followed by a second assessment immediately after 8 weeks of intervention (week 10).

##### Video-based physical activity program

2.4.3.1

The experimental condition will occur daily within regular academic lessons. Students in each classroom will engage in the intervention once a day. The classroom teacher, responsible for conducting the intervention, will choose the appropriate time for implementation. The intervention will not be scheduled during PE lessons or immediately after them, nor during lessons following recess.

The administration of this intervention will use a digital platform accessible to each classroom teacher via a password-protected link.^4^ This platform will facilitate the easy and efficient administration of the video-based PA program. It will feature 10 videos, with five different themes, administered in a randomized manner according to the researcher’s guidelines. However, no theme will repeat throughout the week. To ensure proper use of this tool, classroom teachers will undergo training conducted by the research team before initiating the intervention.

During the intervention, students will follow the instructions in the video and replicate the PA in a gamified format. The structure of the video-based PA program will comprise seven sets of 40-s PA alternated with seven sets of 20-s rest periods, totaling 7 min of intervention with a 2:1 work-to-rest ratio. The PA will target both aerobic and strength-based metabolism, following a strategy with low integration-low relevance movements (Mavilidi et al., 2022).

##### Control group

2.4.3.2

During the 8-week intervention period, the control group will continue receiving usual academic lessons, without the inclusion of PA that may impact their typical levels during school hours.

#### Measures

2.4.4

Each educational agent (teachers, school staff, and students) will be involved in the qualitative aspect of this phase and will undergo evaluation 1 month before and 1 month after the intervention. On the other hand, each student from each participating school will undergo evaluation for quantitative variables both before the intervention (1 week before its start) and after the intervention (1 week following its conclusion).

##### Primary outcome measures

2.4.4.1

###### Cognition

2.4.4.1.1

A cognitive test battery encompassing working memory, cognitive flexibility, and selective attention will be administered to evaluate cognitive functions. All tests used in this study have undergone previous validation for their appropriateness with the children population.

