###### Working memory

2.4.4.1.2

An adapted version of the digit memory test will be used to measure the working memory (Hill et al., 2010). Students will listen to digit sequences and write them down (i.e., 1, 4, 6). If successful, longer sequences will be given until two consecutive failures occur. One researcher dictates while another oversees. This test includes: “Digits Forward,” where participants write the digits in the given order, and “Backward Digit-Span,” where participants write the digits in reverse order.

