###### Cognitive flexibility

2.4.4.1.3

An adapted version of the Trail-making test (TMT) will be used to assess cognitive flexibility (Howie et al., 2015). The TMT will comprise two parts: (a) TMT-A will evaluate processing speed and visual attention, requiring participants to connect numbers from 1 to 25 in order; (b) TMT-B will assess cognitive flexibility by alternating between numbers and letters in ascending and alphabetical order. Students will record completion times using a digital stopwatch displayed on a screen. The test will be supervised by the two researchers. For the Trail Making Test (TMT) used with children, Cronbach’s alpha generally falls within 0.60–0.80 for its subtests, reflecting moderate reliability.

####### Selective attention

2.4.4.1.3.1

The d2, test of attention will be used to assess the selective attention (Brickenkamp, 2012). Students must carefully scan each of the 14 lines of the test from left to right, identifying any “d” with two small lines. These are considered relevant elements, while other combinations are irrelevant. Each line allows 20 s for assessment, with one researcher monitoring time and another ensuring the process runs smoothly. For the d2 in children, Cronbach’s alpha values are generally reported to be between 0.75 and 0.90, indicating strong internal consistency.

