##### Quantitative analysis

2.4.6.1

The outcomes will be analyzed utilizing linear mixed models in IBM SPSS Statistics for Windows, V.20.0 (IBM, Armonk, New York, USA), with significance levels set at *p* < 0.05. These models will evaluate the effects of the condition (video-based PA program and control group), time (pre and posttest), and the interaction between condition and time. Random effects will be incorporated to address the nested nature of the data, adjusting for clustering effects at the school level. Additionally, baseline PA levels, obesity status, gender, and age will be considered as potential moderators in the analysis. Moreover, all assumptions will be tested, and analyses will be adjusted for control variables if necessary.

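### Phase II has three primary cognitive domains, a flat 0.05 level and no rule for success, so neither the 5% error rate nor the 80% power is tied to the effectiveness claim

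*Protocol article*

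**What the plan says.** Section 2.4.4 of the protocol article has a heading "Primary outcome measures" (2.4.4.1). Under it, section 2.4.4.1.1 states: "A cognitive test battery encompassing working memory, cognitive flexibility, and selective attention will be administered to evaluate cognitive functions". The tests then follow:

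- **Working memory (2.4.4.1.2):** a digit memory test with a forward part, "where participants write the digits in the given order, and" a backward part with the order reversed. No total or leading score is named.
- **Cognitive flexibility (2.4.4.1.3):** "The TMT will comprise two parts: (a) TMT-A will evaluate processing speed and visual attention"; only the second part, TMT-B, is said to assess cognitive flexibility.
- **Selective attention (2.4.4.1.3.1):** the d2 test, with no score named.

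Section 2.4.6.1 analyses the outcomes with linear mixed models "with significance levels set at *p* < 0.05". The terms are condition, "time (pre and posttest), and the interaction between condition and time". It does not separate primary from secondary outcomes.

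Section 2.4.1 justifies 138 participants for a single condition-by-time interaction at alpha 0.05, 80% power, f = 0.25 and a correlation of 0.75 between the two measurements. It then sets recruitment at 600.

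Section 2.1 makes effectiveness the primary goal of the trial. The Abstract expects significant improvement in the selected outcomes and links a practical recommendation for schools to the trial proving effective. Neither place says how many outcomes must improve.

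**The concern.** The article fixes several primary outcomes, one uncorrected significance level and a power statement for one test. It does not fix the link between the test results and the conclusion. After the data are in, a significant result in one domain, or in one part of one test, could be presented as the positive primary result. A demand that all domains improve would fit the text equally well. The two readings have very different error rates and power, and the choice between them should not be open once results are known.

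The trail-making test makes this sharper. One of its two parts is described as measuring something other than the primary domain under which it stands, so the set of primary scores has no clear boundary.

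The effectiveness conclusion is to support classroom adoption (Abstract), and trial outcomes are to be extrapolated to Spanish children aged 10 to 12 in government schools (section 2.4.5).

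**Working it through.** **Inputs from the article.** Per-test alpha 0.05 (2.4.6.1; sidedness is not stated, two-sided assumed). Three primary domains (2.4.4.1.1). Five described test parts: digits forward, digits backward, TMT-A, TMT-B, d2 (2.4.4.1.2 to 2.4.4.1.3.1). Power 80% for one test (2.4.1).

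**Input not in the article.** The correlation between scores. It is assumed, and the range 0 to 0.8 is shown.

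**1. The plan's own figure.** The article states no family-wise error rate. Its only related figure is 138 participants for one interaction test. That figure was not reproduced. With f² = 0.0625, m = 2 and r = 0.75, the noncentral F gives:

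- 18 for the within-between interaction, with noncentrality f²·N·m/(1 − r);
- 112 for the between-group effect, with noncentrality f²·N·m/(1 + (m − 1)r);
- 128 for a plain two-group comparison that ignores the correlation.

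The mismatch is a separate matter. What counts here is that the calculation covers one test.

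**2. If any one result counts, differences in either direction.** Under independence the rate is 1 − 0.95^k:

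- k = 3: 1 − 0.95³ = 0.143
- k = 5: 1 − 0.95⁵ = 0.226

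With equally correlated normal test statistics (1,000,000 simulated draws):

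| Correlation (assumed) | 3 tests | 5 tests |
|---|---|---|
| 0 | 14.3% | 22.6% |
| 0.5 | 12.6% | 18.3% |
| 0.8 | 9.9% | 12.7% |

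**3. If any one result counts, differences in favour of the program only.** A false claim of effectiveness needs this direction. One two-sided test at 0.05 gives 2.5%. Under independence:

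- k = 3: 1 − 0.975³ = 0.073
- k = 5: 1 − 0.975⁵ = 0.119

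At correlation 0.5 the rates are 6.3% and 9.2%; at 0.8 they are 5.0% and 6.4%.

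**4. If all must be significant.** The type I error is at most 5%. Power falls instead: with 80% per test and independence, joint power for three domains is 0.8³ = 51%, and higher with positive correlation. The 80% in section 2.4.1 does not describe this rule.

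**5. Cost of a Holm procedure over three scores.** The first step uses 0.05/3 = 0.0167 two-sided. The ratio of detectable effects is (t at 1 − 0.05/6 + t at 0.8) / (t at 0.975 + t at 0.8):

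- 10 degrees of freedom: (2.870 + 0.879) / (2.228 + 0.879) = 1.21
- 18 degrees of freedom: (2.639 + 0.862) / (2.101 + 0.862) = 1.18

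The degrees of freedom are an assumption, because the text at hand does not state the number of schools.

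**The case against.** The strongest reply is that this is a condensed article. Multiplicity control and score definitions are commonly left to an analysis plan, and that plan is not shown. This stands as far as the adjustment method goes: its absence here is not itself a fault. It does not cover which outcome carries the effectiveness claim. That is a protocol choice, and the article makes it by naming three primary domains, setting one flat level and powering one test.

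Three stronger readings are tempting, and the text does not support them.

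- **That the false-claim rate simply is 13% to 23% instead of 5%.** This assumes that any single positive result wins, which the article never says. The hypothesis in the Abstract can equally mean that all selected outcomes improve. The 13% end also needs an assumed correlation of about 0.4 with three tests, and over 0 to 0.8 the rate can be nearer 10%. The range counts harm as well as benefit, so it is roughly twice the rate for a false claim of benefit, and the comparator for that claim is 2.5%.
- **That five scores will each be tested.** The article describes five parts but does not say that each is analysed separately. The digit test could yield one total, and the text already ties cognitive flexibility to TMT-B. Three domains are certain and five is an upper case.
- **That the remark about the trial proving effective is a decision rule.** It is a forward-looking remark in the Abstract.

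It can also be said that 600 recruits far exceed 138 and may restore joint power. That may be so, but the text gives neither the number of schools nor an intraclass correlation, so it cannot be judged.

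**Conclusion.** The point holds in a conditional form. Phase II names three primary domains without a primary score for each and without a success rule, while the significance level and the power statement are those of a single test.

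- If any one domain suffices, the chance of at least one false-positive difference is up to 14% (about 10% to 14% over the assumed correlations), or up to 23% in the upper case of five separate tests.
- For results favouring the program, it is about 7% to 12% under independence, roughly three to five times the 2.5% of one test.
- If all three domains must succeed, the error rate is held, but power under independence would be about 51% when each test has 80%.

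These figures rest on two-sided tests at 0.05 and, away from independence, on assumed equal correlations. The three domains alone carry the finding. An analysis plan that is not shown may already settle it. On the article alone, this should be fixed before outcome data are seen.

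**What to change.** Name one score per domain in advance: for example the backward span, a TMT-B based score (section 2.4.4.1.3 ties only that part to cognitive flexibility) and one specified d2 score. Make the forward span and TMT-A secondary. Test the condition-by-time interaction for the three primary scores with Holm at overall 0.05, with successive thresholds 0.0167, 0.025 and 0.05. Claim effectiveness only for the domains that pass, and base the power statement on that rule. Requiring all three domains, or a single composite, would also be acceptable if stated beforehand with power to match.

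The change is wording in the protocol and analysis plan, with no new data collection. The cost is sensitivity: the detectable effect at the first Holm step rises by about 18% (18 degrees of freedom) to 21% (10 degrees of freedom). This should be recalculated once the number of schools is fixed.
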